### Intervention

#### Acupotomy group

The patients will be placed in a supine position with the knees flexed 30 ~ 45°. A cushion will be placed beneath the knees. The physicians will select 6 points from a point set, as follows. The point set contains 8 points, including the upper and lower points of the medial collateral ligament of the affected knee joint, the upper and lower points of the lateral collateral ligament, the subpatellar ligament points, the upper point of the patella, the muscle insertion point of the popliteal muscle, and the medial popliteal fossa stimulation points. We will stimulate 6 points for unilateral knee pain and 12 points for bilateral knee pain (Table 1).

**Table 1 Tab1:** Location of point set

Point name	Location
The upper point of the medial collateral ligament	A lateral tubercle located at the medial condyle of the femur
The lower point of the medial collateral ligament	The posterior part of the liriodendron area located at the medial condyle of the tibia
The upper point of the lateral collateral ligament	A lateral tubercle locating at the lateral condyle of the femur
The lower point of the lateral collateral ligament	The apex of the capitula fibula
The subpatellar ligament points	The lower part of the patellar ligament
The upper point of patella	Directly above the patellar bottom and located in the deep surface of the quadriceps tendon
The insertion of popliteal muscle	Located behind the upper part of the medial tibia
The medial popliteal fossa stimulation points	Located at the medial wall of the popliteal triangle, between the semitendinosus and semimembranosus’ muscles

After standard disinfection, the physicians will operate a Hanzhang type I no. 4 straight needle-knife (Beijing Huaxia Needle Knife Medical Equipment Factory) to perform acupotomy (Fig. 2). Physicians selected will have more than 5 years of experience and will be retrained for 16 h before the study begins.

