### Safety monitoring

To protect the rights and interests of patients, all patients will be informed of the potential benefits and risks of the trial before they enroll. After confirming that the patient understands the relevant content, we will ask the patient to sign an informed consent form. Patients who do not sign the informed consent form will not be admitted to the study.

Acupotomy may trigger adverse events, including dizziness and local hematoma. If dizziness occurs during treatment, the doctor will stop the treatment immediately. Then, the doctor will lay the patient down on the pillow and provide warm water. If hematoma occurs, the patient will be instructed to apply a local cold compress and switch to a hot compress after 24 h to promote dissipation and absorption of the blood. If an adverse drug reaction occurs, the drug will be discontinued. Active clinical observation and symptomatic treatment will be carried out.

The Ethics Committee of the First Affiliated Hospital of Guangzhou University of Chinese Medicine will monitor the safety of this trial and provide advice (e.g., endpoint adjustment) if necessary. When an adverse event occurs in a patient, the researchers will record the details, such as the time, severity, duration, treatment measures, and event outcomes. The responsible doctor will determine the causal relationship between the treatment method and the adverse event and decide whether the patient will be allowed to continue the study. Relevant information will be reported to the ethics committee on the same day.

The following are the criteria for terminating a patient from the study: (1) the patient has experienced a serious adverse event, the patient has requested to suspend participation in the trial, or the trial operator believes that it is necessary for the patient to be terminated from the trial; (2) during the study, the patient is found to have a systemic disease that could not be detected before the start of the clinical trial; (3) for other reasons, the researchers believe that the patient is not suitable for continued treatment; and (4) the patient has privately received other interventions that may affect the outcomes.

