### Statistical analysis

Per-protocol subject analysis and intention-to-treat analysis will be used to analyze the efficacy. The safety analysis set will be used to perform the safety evaluation.

We will develop a statistical analysis plan with a statistician. The statistical software package R 3.4.3 will be used to perform a descriptive statistical analysis, exploratory analysis, and dropout analysis. The results will be considered statistically significant when the *P* value is less than 0.05. In the intention-to-treat analysis, when data are missing, the last observation will be used for interpolation. Then, we will perform a sensitivity analysis for the result.

For continuous variables that follow or meet the assumptions of a normal distribution and homogeneity of variance, we will use Student’s *t* test; otherwise, the Mann-Whitney test or Wilcoxon test will be used. A chi-square test will be performed for discrete or categorical variables. When analyzing data obtained by repeated measurements, we will use analysis of variance or analysis of covariance.

For the safety analysis, we will first perform a descriptive analysis. Subsequently, the incidence of adverse reactions will be compared between the two groups using a chi-square test. Causality will be considered in the comparison regarding the severity of adverse reactions and the needle-knife operation. If there are a large number of adverse reactions, the relationship between the intervention time and baseline characteristics will be analyzed. We will use the correlation coefficient to analyze these relationships.

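### The conditional follow-up safety analysis correlates intervention time with baseline characteristics and leaves out the adverse reaction, so as written it cannot show who is at risk

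*Protocol article*

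**What the plan says.** The safety paragraph of the Statistical analysis section has four steps.

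1. A descriptive analysis.
2. A between-arm comparison: "the incidence of adverse reactions will be compared between the two groups using a chi-square test".
3. A statement on severity and the procedure: "Causality will be considered in the comparison regarding the severity of adverse reactions and the needle-knife operation".
4. A conditional step: "If there are a large number of adverse reactions, the relationship between the intervention time and baseline characteristics will be analyzed". The method follows: "We will use the correlation coefficient to analyze these relationships".

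Two other places bear on the point. Under Safety monitoring, for each adverse event, "the researchers will record the details, such as the time, severity, duration, treatment measures, and event outcomes". Under Acupotomy group, exposure depends on laterality: "We will stimulate 6 points for unilateral knee pain and 12 points for bilateral knee pain".

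**The concern.** In the fourth step the adverse reaction appears only in the opening condition. The variables then related to each other are the intervention time and the baseline characteristics, and neither is a harm. The question a reader would want answered once reactions accumulate is which patients have them and whether more exposure brings more of them. The stated correlation does not address it.

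The Discussion presents the trial as an evaluation of safety as well as efficacy, and Safety monitoring names dizziness and local hematoma as events the procedure may cause. If such events became frequent, an analyst following the text would produce a table with no bearing on them. An analyst who departed from it would be choosing outcome, predictors and method after seeing the data. The trigger, "If there are a large number of adverse reactions", has no threshold, which adds to that freedom.

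**Working it through.** **The plan's own figures.** The article gives no figure for this step and no expected adverse-event rate, so there is nothing to reproduce. The sample-size calculation does not enter. The only design inputs used below are 136 enrolled and 1:1 allocation, hence 136 / 2 = 68 per arm.

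**Step 1: what each safety analysis relates.**

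| Planned analysis | Contains the adverse reaction? | Contains patient characteristics? |
|---|---|---|
| Incidence by arm, chi-square | yes | no |
| Severity and the needle-knife operation | yes | no |
| Correlation, if reactions are many | only as trigger | yes, against intervention time |

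No row has the reaction on one side and patient characteristics on the other, and no other section of the article supplies one.

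**Step 2: what the literal analysis can detect.** This is an illustration, and all its inputs are assumptions except the 136 patients.
- Baseline factor x and intervention time t are independent standard normal variables.
- The probability of a reaction is 1 / (1 + exp(−(−1.4 + ln(OR)·x))), which is 1 / (1 + exp(1.4)) = 19.8% at x = 0.
- The correlation is tested two-sided at 5%, so the critical |r| is 1.978 / √(134 + 1.978²) = 0.168.
- There are 4,000 runs per row, so the simulation standard error near 5% is √(0.05 × 0.95 / 4000) = 0.3 percentage points.

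| Odds ratio per SD of x | Time against baseline factor (as written) | Reaction against baseline factor |
|---|---|---|
| 1 | 4.8% | 5.8% |
| 2 | 5.5% | 88.9% |
| 4 | 5.3% | 100% |

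The analysis as written stays at its false-positive rate however strongly the factor predicts harm. This follows from the algebra: the reaction does not enter the statistic.

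**Step 3: the exposure variable.** Intervention time is not defined. If it means length of course, the intervention text fixes two weekly sessions in both arms, so it would vary little. (Table 2 labels the treatment period W1-W6, a separate inconsistency that needs reconciling.) The exposure that clearly varies under the protocol's own rule is 6 or 12 points per session, that is 2 × 6 = 12 or 2 × 12 = 24 over two sessions.

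**Step 4: the between-arm test, a minor matter.** With a of 68 against 0 of 68, chi-square = N(ad − bc)² / (product of the four margins). The corrected version replaces |ad − bc| by |ad − bc| − N/2.
- 4 v 0, uncorrected: 136 × 272² / (68 × 68 × 4 × 132) = 4.12, P = 0.042. Corrected: 136 × 204² / (68 × 68 × 4 × 132) = 2.32, P = 0.13. Fisher: 2 × C(68,4) / C(136,4) = 0.12.
- 5 v 0, uncorrected: 136 × 340² / (68 × 68 × 5 × 131) = 5.19, P = 0.023. Corrected: 136 × 272² / (68 × 68 × 5 × 131) = 3.32, P = 0.068. Fisher: 2 × C(68,5) / C(136,5) = 0.058.

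Expected event counts are 2 and 2.5 per arm, below the customary 5. The conclusion at 5% depends on whether a correction is applied, which the article does not state.

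**The case against.** The strongest reply is that this is a slip of wording. The sentence sits in a safety paragraph and opens with adverse reactions, and the next sentence speaks of relationships in the plural. The likely intention was to relate reactions to intervention time and, separately, to baseline characteristics. On that view few analysts would program the literal version. The step is also conditional and exploratory, and an analysis plan is announced. This largely stands as to intent and importance. It does not remove the point: an announced plan excuses missing detail, but this is a stated analysis with the wrong variables, and a plan written to match it would inherit them.

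A reader might infer several stronger things that the documents do not support.
- **That the trial has no usable safety analysis.** The between-arm incidence comparison has the right outcome. Event details are recorded, causality is judged case by case, and events go to the ethics committee the same day.
- **That the procedure is ignored as a source of harm.** The sentence on severity and the needle-knife operation is vague, but it exists.
- **That treating both knees nearly doubles the risk.** With an assumed constant, independent risk of 0.5% per penetration, 1 − 0.995^12 = 5.8% and 1 − 0.995^24 = 11.3%. The near-doubling comes from the assumption and is not evidence from this trial. A table by number of points is also something an article may leave to the analysis plan.
- **That the chi-square test will produce a false safety signal.** That needs sparse events, for which the article gives no rate, and an uncorrected test, which it does not specify.

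**Conclusion.** The point holds for the conditional follow-up analysis: taken as written, "the relationship between the intervention time and baseline characteristics will be analyzed" cannot identify who is at risk of an adverse reaction, and no other section corrects it. That conclusion rests on the wording alone. The simulation only illustrates it and depends on an assumed 20% risk, one baseline factor, and intervention time independent of that factor.

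The size is small to moderate. The main between-arm safety comparison and all efficacy analyses are untouched, and the slip is probably unintended. It is still worth correcting, because the text as it stands would be followed, or silently replaced, at the moment when harms had proved frequent. The choice of test for sparse counts is a secondary improvement and does not carry the point.

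**What to change.** Replace the two sentences with wording such as: *In exploratory analyses, the occurrence and severity of adverse reactions will be tabulated within each arm by intervention exposure (including unilateral or bilateral treatment, that is 6 or 12 points) and by pre-named baseline characteristics, whatever the number of reactions. Where the number of events allows, occurrence will be related to these factors by penalised or exact logistic regression.* Define intervention time or drop the term. Tables can be produced at any count, whereas a model with several covariates is not supportable on a handful of events, so state the minimum event number in the analysis plan.

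As a minor addition, report the between-arm risk difference with a confidence interval and use Fisher's exact test when expected counts are small.

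The cost is one or two sentences, a few more tables and a slightly conservative test. The article does not say that the number of points treated is recorded. Laterality has to be known in order to apply the 6-or-12 rule, but the sponsor should confirm that it is captured on the case report form for both arms.

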## Discussion

KOA is a chronic disease involving pain, swelling, stiffness, restricted movement, popping, or deformity [29]. It is associated with sex, age, body weight, physical activity, occupation, and biochemical factors [30]. KOA usually occurs in females or elderly individuals. Most KOA patients are overweight or obese. One in every seven cases of KOA is attributable to work, which indicates that occupation is associated with KOA.

There are three views regarding the pathological mechanism of KOA [31]. First, mechanical loading is considered to cause changes in biological stress, which can damage knee cartilage. Furthermore, synovial inflammation is considered to induce matrix metalloproteinase overexpression in cartilage, which can also damage knee cartilage. In addition, some adipokines, such as leptin and adipsin, are known to contribute to the pathological mechanism in terms of triggering cartilage impairment.

The guideline has provided different recommendations for KOA in clinical practice [32]. Physicians always use paracetamol (acetaminophen) and nonsteroidal anti-inflammatory drugs (NSAIDs) (celecoxib, indomethacin, etc.) to address KOA symptoms, according to the guidelines [4, 33–35]. However, patients cannot use these drugs for extended periods. Paracetamol (acetaminophen) does little to improve patients’ pain, stiffness, and reduced physical function [36]. In addition, paracetamol (acetaminophen) causes hepatotoxicity [37] and adverse reactions in the kidney, cardiovascular system, and gastrointestinal tract with long-term use [38]. NSAID use also increases the risks of adverse cardiovascular outcomes [39] and upper gastrointestinal complications [40]. Hence, nonpharmacological therapies play an essential role in treating KOA [41]. There have been some clinical studies of traditional Chinese medicine strategies in treating KOA, such as acupuncture [42], moxibustion [43], tai chi, and massage [44]. Compared with other nonpharmacological therapies, acupotomy is a better choice for the treatment of KOA. It can be applied less frequently, which is good for patient compliance. In addition, acupotomy can not only relieve pain but also improve joint mobility.

As a special type of acutherapy, acupotomy can improve KOA symptoms via different pathways. Acupotomy can restore the biomechanics of the knee by reshaping the physical environment in the knee [45]. Acupotomy can also curb inflammation [46, 47]. The reduction in IL-1β, IL-6, and TNF-α suppresses the expression of MMP-1, MMP-3, and MMP-13, which is conducive to preserving knee cartilage. In short, acupotomy promotes chondrocyte repair and regulates cartilage metabolism [48].

Clinical research has been performed to evaluate the efficacy of acupotomy in treating KOA [9, 10]. However, the design of both of these former trials was inadequate. In both studies, acupuncture was selected as a comparison, which failed to demonstrate the powerful efficacy of acupotomy. One study [11] used inappropriate randomization procedures and did not use blinding, while another [12] had a small sample size and used only a scale as an outcome. Thus, we designed a stricter study to explore the efficacy and safety of acupotomy in treating KOA with sham acupotomy as a comparison. In addition, to the best of our knowledge, this will be the first single-blind study on acupotomy. Moreover, we will also use clinical outcomes (WOMAC, VAS score, joint mobility and quality of life) and surrogate outcomes (musculoskeletal ultrasound findings, X-ray examination findings, plantar pressure distribution testing, maximum knee circumference).

Our exclusion criteria are relatively strict and may exclude many patients in clinical practice. In this manner, we will be able to enroll patients without many confounders, and the results will represent a powerful conclusion regarding the internal validity of this study. However, the external validity of this trial is not strong, which means the data may not be eligible for extrapolation.

This study will have some limitations. First, we will only enroll patients with level I-III KOA; thus, we will not be able to observe the effect of acupotomy on KOA of other levels in patients. Second, we selected a relatively short-term follow-up period for evaluating a chronic arthritis condition, preventing the monitoring of long-term effects. Third, this will be a single-blind study, which means we will not be able to avoid caregivers’ impact. Furthermore, as we will use the last observation carried forward method to interpret findings, if the rate of missing data is high, the stability of the data analysis results after interpolation will become low, potentially even distorting the results of the original data analysis due to bias. Last, this study will be performed in China, so the conclusion may not be suitable for application in patients of other ethnicities.

In summary, we will perform a parallel, block-randomized, single-blind, sham-controlled trial to evaluate the efficacy and safety of acupotomy in KOA patients.

## Trial status

This study will begin in June 2020. The study protocol is version 3.0 (2020.4.27). We will recruit participants from June 1, 2020, to June 30, 2022.

## Data Availability

Not applicable. We have no datasets included in this study protocol. In this research, volunteers will provide informed consent to ensure that data regarding blood indicators can be used in this study, and these data are not applicable to other channels. The results of this study will be communicated with others via a peer-reviewed journal. The full protocol will be accessible upon reasonable request after the trial is complete.

## Abbreviations

KOA: Knee osteoarthritis
WOMAC: Western Ontario and McMaster Universities Osteoarthritis Index
VAS: Visual analog scale
CRF: Case report form
SF-36: 36-Item Short-Form Health Survey
